### Statistical analysis

2.14

Statistical analysis will be performed using only the data obtained from the patients who complete the study. The Kolmogorov–Smirnov test will be applied before the analysis of the normality of each parameter. The *t* test will be used to compare all means. All tests will be performed using Graphpad Prism 5 (Graphpad Software, San Diego, CA). Data will be presented on average and ±standard deviation. The level of significance will be set at *P* < .05.

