The PDT is a therapeutic option in many fields of medicine.^[19]^ It is selective and noninvasive, also indicated for transplant and oncology patients.^[15]^ It consists of the combination of a chromophore agent, such as methylene blue, at a certain concentration, associated with monochromatic laser light at a given wavelength.^[20]^ The photosensitizer (methylene blue) absorbs visible laser light at a suitable wavelength (660 nm) from the ground state to the singlet state, which has a short shelf life. From there, the photosensitizer can lose energy through nonradioactive, radioactive (phosphorescence) processes, or generate reactive oxygen species (ROS) through 2 mechanisms: either by electron transfer, forming free radicals (type I reactions), or through the transfer of energy to molecular oxygen forming singlet oxygen (type II reactions).^[21]^ The lesions of herpes labialis are recurrent in some patients, causing pain, aesthetic commitment, and absenteeism in the work. Your complete remission lasts until 15 days. Treatment with acyclovir decreases painful symptoms; however, it causes viral resistance and does not prevent recurrence of the lesions. It is known that antimicrobial PDT (aPDT) has numerous advantages among them the reduction of the time of remission and, moreover, does not cause resistance; although there are still no well-designed clinical studies that prove its effectiveness, there are only case reports. Therefore, the objective of this study will be to evaluate whether PDT is able to reduce the healing time of these lesions and decrease their recurrence.

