### Sample size calculation

2.1

The sample was calculated using standard error type 1 of 0.2 and 95% confidence level as indicated in the literature.^[22–27]^ The calculation is consistent, equivalence tests in nonparametric models of survival (Kaplan and Meier, 1958). The survival function, at a given time *t*, can be estimated from observed survival times, relative to the proportion of individuals who survived beyond time *t*. In our case, time *t* is defined as the treatment date, and survival is estimated in days until recovery of the patient. Based on the survival analysis methodology, a sample of 24 participants (12 per group) was calculated. The estimation of differences between groups will be done based on the Kaplan–Meier estimator or limit product estimator.

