### Study variables and time

2.12

The primary study variable will be evaluation of the resolution time of the lesions in days (primary objective of the study). For this, a 15-day follow-up will be performed for this variable.

The secondary variables of the study will be

Follow-up of the recurrences of herpes simplex labialis (HSL) lesion at baseline (T0), 1 (T3), 6 months (T4), and 1 year (T5) follow-up periods.Presence of ballooning cells by exfoliative cytology at baseline (T0) and 3 (T1) days after injury.Evaluate if the amount of HSV-1 decreases after treatment with aPDT by Quantitative polymerase chain reaction q at the baseline (T0), 3 (T1), and 7 (T2).Evaluation of cytokines interleukin (IL)-6, IL-1β, IL-8, tumor necrosis factor alpha (TNF-α), and IL-10 by enzyme-linked immunosorbent assay method in nonstimulated saliva and HSL lesions in the baseline (T0), 3 (T1), 7 (T2), and 30 days after treatment (T3).To verify the presence of pain in HSL patients by HSL VAS at baseline (T0), 3 (T1), 7 (T2), and 30 days after treatment (T3).Check the temperature at the site of HSL lesion at baseline (T0), 3 (T1), 7 (T2), and 30 days after treatment (T3).Quality of life perception of HSL patients related to oral health will be assessed using the OHIP-14 questionnaire at baseline (T0) and 30 (T3) days after treatment.

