#### Evaluation of injury resolution time in days

2.13.1

The patients will be followed up in 3 and 7 days and the resolution of the lesion will be monitored until it is completed. The completed will be accompanied by photos and telephone contact and noted in a specific clinical file. For this, a 15-day follow-up will be performed for this variable.^[15]^

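### Section 2.1 bases the comparison of time to lesion resolution on Kaplan–Meier methods, but section 2.14 names only a t test on means among completers, with no rule for lesions unresolved at day 15

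*Protocol article*

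**What the plan says.** - **Primary outcome.** Section 2.12: "The primary study variable will be evaluation of the resolution time of the lesions in days", and "a 15-day follow-up will be performed for this variable".
- **Follow-up.** Section 2.13.1 first says that "the resolution of the lesion will be monitored until it is completed" and then, in the same paragraph, "For this, a 15-day follow-up will be performed for this variable". The Introduction says of the lesions: "Your complete remission lasts until 15 days".
- **Sample size.** Section 2.1 applies survival methodology to days from treatment to recovery, arrives at 12 per group, and states: "The estimation of differences between groups will be done based on the Kaplan–Meier estimator or limit product estimator".
- **Analysis.** Section 2.14 limits the analysis to patients who complete the study, checks normality, says that the t "test will be used to compare all means", and reports mean and SD. It names no survival method and does not mention the primary outcome separately.

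**The concern.** The article does more than leave the method to a fuller plan. It states how the groups will be compared in two places, and the two do not match. Someone following 2.14 literally would compare mean resolution times with a t test. Someone following 2.1 would draw Kaplan–Meier curves. If this is still open when the data are seen, the choice can be made on the result.

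The methods also treat incomplete times differently. For a lesion open at the end of follow-up, or a patient lost before healing, it is known only that resolution took longer than the time observed. Kaplan–Meier and log-rank methods use that information. A t test needs a number for every patient, so the patient is either left out or given a value. Those left out are the slow healers, and if one treatment heals faster, more of them sit in the other arm. The estimated difference then shrinks and power falls, in a trial sized at 12 per group.

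**Working it through.** **1. The two sections side by side.**

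| Item | Section 2.1 | Section 2.14 |
|---|---|---|
| Quantity | days from treatment to recovery | means of the parameters, not listed |
| Method | Kaplan–Meier estimator | t test |
| Incomplete times | usable by the method, no rule given | no rule given |
| Patients | not stated | completers only |

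Kaplan–Meier is an estimator, not a test, so 2.1 names no test either.

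**2. The plan's own figures.** The dropout allowance reproduces: 12 / (1 − 0.20) = 15 per group, 30 in total. The 12 per group does not, because no effect size is given. If all 24 patients resolve, a two-sided 5% log-rank test with 80% power needs, by Schoenfeld's formula, ln(HR) = 2 × (1.960 + 0.842) / √24 = 1.144, a hazard ratio of about 3.14.

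**3. Share unresolved at day 15 (assumed healing times).** Assume lognormal times with coefficient of variation 0.4. Then σ² = ln(1 + 0.4²) = 0.148, σ = 0.385, and for mean m, μ = ln(m) − 0.074. The share unresolved is 1 − Φ(z), with z = (ln 15 − μ) / σ. For m = 10: z = (2.708 − 2.228) / 0.385 = 1.245, which gives 10.7%. Means of 7, 8, 11 and 12 days give 1.5%, 3.4%, 15.9% and 22.0%.

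**4. Effect of dropping open lesions.** The mean among lesions resolved by day 15 is m × Φ(z − σ) / Φ(z).
- Control mean 10: 10 × 0.805 / 0.893 = 9.01.
- Photodynamic therapy (PDT) mean 7: 7 × 0.963 / 0.985 = 6.84.
- Difference: 9.01 − 6.84 = 2.17 days, against a true 3.

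**5. Simulation on the same model.** 12 per arm, whole-day times, cut-off at day 15, 3,000 runs, two-sided 5%.

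| Assumed means, control/PDT | Control unresolved | Difference: true / dropped / set to 15 | Power: t, dropped / t, set to 15 / log-rank |
|---|---|---|---|
| 7/5 | 1.5% | 2.0 / 1.9 / – | 50 / 51 / 50% |
| 8/5 | 3.4% | 3.0 / 2.7 / – | 76 / 80 / 79% |
| 10/7 | 10.7% | 3.0 / 2.2 / 2.6 | 48 / 58 / 56% |
| 11/8 | 15.9% | 3.0 / 1.9 / 2.5 | 34 / 48 / 47% |
| 12/9 | 22.0% | 3.0 / 1.6 / 2.2 | 25 / 40 / 40% |

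The dropped differences in the first two rows come from the formula in step 4. The simulation standard error of a power figure is at most √(0.25 / 3000) = 0.9 points.

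**6. A second model.** Weibull times with assumed shape 2.5 and assumed hazard ratio 3.2, 12 per arm, 2,000 runs.

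| Control unresolved | Difference: true / dropped / set to 15 | Power: t, dropped / t, set to 15 / log-rank |
|---|---|---|
| 10% | 3.5 / 2.7 / 3.3 | 54 / 67 / 74% |
| 20% | 4.1 / 2.4 / 3.4 | 39 / 65 / 75% |
| 40% | 5.2 / 1.7 / 3.2 | 18 / 59 / 70% |

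With no treatment effect, all three methods reject in about 5% of runs (4.6% to 6.2% across scenarios).

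**7. What setting to day 15 estimates.** If no one is lost earlier, the mean with open lesions set to 15 is exactly the restricted mean time to day 15. Its gap from the unrestricted difference reflects a different quantity, not an error in estimating the restricted one.

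**The case against.** **The sections can be read together.** Section 2.14 does not mention the primary outcome, and 2.1 does. One may read Kaplan–Meier as meant for resolution time and the t test for the outcomes summarised as means. That reading is tenable, and a reader should not infer that the plan labels two rival primary analyses. But 2.14 is the only analysis section, covers all means, carves nothing out and omits the survival method, so the text still has to be settled.

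**Censoring may be rare.** Section 2.13.1 says monitoring continues to resolution, which would leave few censored times. The Introduction puts remission at up to 15 days, the clock starts at treatment, ulcers and crusts are eligible, and controls receive acyclovir, which the article says shortens the episode. All of this points to a low unresolved share, perhaps nearer the first two lognormal rows. That stands as a limit on the size of the harm. It does not remove the point, because the same paragraph of 2.13.1 also fixes 15 days and patients can be lost before healing.

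**The plan does not say open lesions are dropped.** Correct. A patient with an open lesion at day 15 who stays in follow-up is still a completer. The larger losses apply only if such lesions are excluded.

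**Setting to 15 is not wrong in itself.** Also correct. It loses no power in the lognormal model and about 7 to 11 points in the Weibull model, so the cost depends on the assumed distribution.

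**Secondary outcomes.** A reader might infer that the t test is also misapplied to ballooning cells and recurrences, or object that the normality check has no stated consequence. Section 2.13.3 speaks of quantifying the cells, and such detail is commonly left to the full plan. These are not part of the point.

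**Conclusion.** The point holds as an inconsistency in how the article fixes the primary comparison: survival methods in 2.1, only a t test on completers' means in 2.14, and no rule for a lesion open at day 15 or a patient lost before healing. This needs no assumption.

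The size of the harm does rest on assumptions. Under lognormal times it is negligible at 1.5% of control lesions unresolved. At 10.7% to 22.0%, dropping them removes 27% to 47% of a true 3-day difference (0.8/3 to 1.4/3) and costs 8 to 15 points of power against the log-rank test. Under the Weibull model the power loss from dropping is about 20 points at 10% unresolved and 35 at 20%. The healing distributions, effect sizes and unresolved shares are all assumed; the document gives none of them.

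A reader might infer that the t test will produce false positive findings, or that 10% to 22% unresolved is to be expected. Neither is supported. Type I error stays near 5% for any one method fixed in advance, and nothing in the article gives the unresolved share. The risks are dilution, lost power and a choice of method after seeing the data.

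**What to change.** In 2.14, name one primary analysis that agrees with 2.1:
- Kaplan–Meier curves of time to resolution from the treatment date, compared with a log-rank test.
- Lesions unresolved, and patients lost before resolution, censored at their last assessment rather than excluded as non-completers.
- The effect in days given as the median and/or the restricted mean time to day 15, with 95% confidence interval.
- The t test kept for continuous secondary outcomes.

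In 2.13.1, reconcile the two follow-up statements: either resolution is followed to completion, or observation for this outcome ends at day 15. Carry the same statement into 2.12.

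The cost is a few sentences. No further patients or data are needed, and the methods are standard in ordinary statistical software. The change should be made before unblinding.

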## Discussion

3

Oral herpes lesions are very painful, bringing discomfort, and aesthetic impairment.^[6,10]^ The causes of recurrences are uncertain,^[39]^ the gold standard treatment is with antiviral acyclovir,^[9]^ and it is the most commonly used to prevent or suppress VHS^[10,14,40]^ but continued use of this drug may cause high viral resistance.^[7,10]^ Antiviral medications are most effective when the patient uses them for prodromal symptomatology and acyclovir is effective in reducing the duration and symptoms of infection, but the optimal dose is still unknown.^[9]^ Acyclovir may reduce the duration of symptoms but does not prevent recurrence.^[15]^ Because of these factors, aPDT is a good alternative for the treatment of herpetic lesions, which is a very promising treatment modality. Marotti et al^[20]^ in their study with 4 participants in the vesicle phase performed their perforation with a sterile needle to cause the flow of liquid. A 0.01% methylene-blue-soaked cotton ball was placed over the lesion for 5 minutes and the excess photosensitizer was removed. The lesions were irradiated with a wavelength of 660 nm, spot size 0.04 cm^2^ in continuous mode. The power was 40 mW, 2 minutes per point, with energy of 4.8 J (total energy of 19.2 J). After 24 hours, 72 hours, and 1 week, the same wavelength was used changing the parameters, with energy density of 3.8 J/cm^2^, 15 mW, and 0.6 J. No discomfort was reported throughout treatment and follow-up was 6 months with satisfactory results. Ramalho et al^[29]^ reported 2 cases, 1 in a 28-year-old female with a vesicle lesion, in which was punctured, its contents absorbed with absorbent paper, 0.005% methylene blue placed, waiting time of 5 minutes for the photosensitizer to act and the laser applied at a wavelength of 660 nm, with a power of 100 mW, 4.8 J, for 2 seconds per point. The following day, the lesion was already in the crusting phase. The 2nd case reported was from a female participant, 30 years old, who presented in the prodromal or tingle stage, and the participant reported that she had used acyclovir cream 5% when she had prodromal symptomatology. Methylene blue was placed over the macula and the same parameters as in the 1st case were used. The participant was instructed to continue acyclovir cream every 4 hours, and after 24 hours of PDT application, the macula was no longer detectable and herpes lesion did not develop. Marotti et al^[18]^ conducted a study with high intensity laser and PDT. The first case using PDT was in a 23-year-old female with herpetic lesions in the vesicle phase. They were punctured, dried with sterile gauze and 0.001% methylene blue and laser was applied with wavelength 660 nm, with fluency of 100 J/cm^2^, power of 100 mW, 28 seconds, 2.8 J of energy, spot size of 0.028 cm^2^ with total energy of 8.4 J after 24, 48, 72 hours, and 7 days after the 1st application. The parameters used were 20 J/cm^2^, power of 40 mW, 14 seconds per point with energy of 0.56 J per point. The other case was with a 24-year-old male participant using the same parameters as the previous case. Based on these cases and the cases in which Marotti et al^[20]^ used high intensity laser, the authors concluded that PDT has the advantage of low cost. It is based on the interaction of a photosensitizer and laser light in the tissue, causing selective cell damage, generating ROS.^[13]^ The photosensitizer (methylene blue) absorbs visible laser light at an appropriate wavelength (red 660 nm) from the ground state to the singlet state, which has a short lifespan. From this, the photosensitizer can lose energy through nonradioactive processes (phosphorescence) or generate ROS through 2 mechanisms: either by electron transfer, forming free radicals (type I reactions) or by transfer of energy to molecular oxygen forming singlet oxygen (type II reactions).^[21]^ The antimicrobial PDT is an effective alternative to the gold standard treatment, acyclovir, but there are no clinical studies yet to prove the efficacy of PDT in patients with recurrent herpes lesions, only case studies.

This study will be a double-blind clinical trial with the goal of not inducing the researcher who will treat the patient to a positive aPDT result as well as to mask the participant's type of treatment. Blocked randomization was performed so that if there is any interruption of work for any reason, we will have groups with proportional numbers of participants, allowing comparison between them. After approval by the Research Ethics Committee of the Universidade Nove de Julho, patients will be invited to participate in the study by signing the ICF. If the lesions are in the vesicle stage, they will be topically anesthetized with 2% lidocaine gel, as directed by the Research Ethics Committee. Exfoliate cytology of the lesions will be performed as it is a simple and reliable method of confirming HSV infection, according to Barret et al. Microscopically we can observe changes in cytoplasm and nuclear structures. Lange et al,^[41]^ observed that cells exhibit a space between inclusion and the extended “bull's eye” cell membrane. In addition, he observed little frequency of ballooning cells, which are pathognomonic cells in herpes lesions.

Unstimulated saliva collection will be performed before treatment, 3, 7, and 30 days after the procedure, in both groups, to quantify the virus by qPCR and to evaluate the cytokines IL-6, IL-1β, IL-8, TNF-α, and IL-10. For HSV-1 amplification by qPCR, a set of HSVP1/HSVP2 primers will be used, which corresponds to DNA sequencing the eight human herpes virus described by Johnson et al. This primer amplifies HSV-1 subtypes, HSV-2, Epstein-Barr virus, and cytomegalovirus.^[32,33,42]^

In addition, the inflammatory markers TNF-α, IL-1β, IL-6, and IL-8 and IL-10 will be determined by 8-plex high sensitivity human cytokine per Millipore (Millipore Corporation, Billerica, MA), where Marques Filho et al^[43]^ found high levels of these cytokines in the crevicular fluid of patients with peri-implantitis. In the experimental group, methylene blue will be delicately placed and with a 1-minute wait for the photosensitizer to interact with the tissue according to Alvarenga et al.^[43]^ The parameters used for laser application will be performed according to Ramalho et al^[29]^ in case studies reported using 0.005% methylene blue photosensitizer, with the laser head in contact with the lesion, perpendicularly, 3 J energy for 30 seconds, with diode laser at 660 nm wavelength in a single session. Marotti^[20]^ used the laser at the same wavelength, with an energy density of 120 J/cm^2^, with a power of 40 mW, with 2 minutes per point and 4.8 J energy at each point and with 4 points around the lesion in herpes lesions in the vesicle phase, breaking them prior to the application of methylene blue, in which it was used at a concentration of 0.01% (the use of 0.005% is explained based on the large quantity of works with good results). The total energy delivered was 19.1 J. Twenty-four hours after the 1st application, the procedure was repeated, but with energy density of 3.8 J/cm^2^, 15 mW of power, with 0.6 J of energy at the same previously irradiated points, and these parameters were repeated after 72 hours and after a week. There was a decrease in the frequency of vesicle recurrence. De Paula Eduardo et al,^[13]^ found in a literature review that in cases where aPDT was indicated in the vesicle phase, there was a reduction in vesicle title as well as lesion duration. Decreased signs of infection and symptoms are reported within hours of aPDT application, provided they are used at a wavelength around 660 nm and with the appropriate photosensitizer. Based on these studies, we expect a reduction in the time of resolution of lesions, as well as the recurrence of lesions, providing a low cost alternative indicated for patients with viral resistance to the gold standard drug, acyclovir, and, offering an alternative in immunocompromised patients who have a high recurrence of herpetic lesions and in patients who should avoid drug administration by organ impairment where acyclovir is metabolized, as well as in healthy patients who have a high recurrence of lesions, decreasing discomfort.
